### Stopping rules

When consensus is reached for a given item, no subsequent ranking rounds for that item will be performed. Consensus items that are considered equivocal, in addition to remaining non-consensual items, will be further deliberated during the consensus meeting.

### Round 1

Panellists will be invited to rate their level of agreement with candidate items generated from scoping review results and consultation with the study executive group. Free-text boxes will be included for panellists to provide feedback or identify additional candidate items to be included in the next e-Delphi survey round.

### Round 2

Regardless of whether they participated in the previous round, panellists will be invited to participate in Round 2 of the e-Delphi survey. All panellists will be invited to rate new items and re-rate previous items that did not reach consensus. When re-rating their level of agreement, panellists will be presented with their previous round scores alongside the aggregate group results. Anonymous feedback from Round 1 will also be compiled and presented during Round 2. Any newly suggested items during Round 2 will be deliberated during the consensus meeting.

### Summary panellist characteristics

At the start of the e-Delphi survey, panellists will provide basic demographic details to ascertain their discipline subgroup, ensuring they receive the correct list of candidate items. To maintain anonymity, this demographic data will not contain identifiable information, and only aggregate responses of 5 or more panellists will be analyzed. We will report aggregate panel characteristics based on gender, discipline group or subgroup (depending on the number of panellists), level and type of experience, country income level, and World Bank work regions.

### Quantitative analysis

We will report response rates, agreement levels, consensus, and stability across rounds using median, range, and IQR for each criterion item. The proportion of panellists who skipped items or selected “not qualified to respond” will be reported. Fisher’s exact test will be used to evaluate differences in item ratings by panellist characteristics: primary panellist disciplines (see S2 Table), country income level (high-income versus low-and-middle income), and World Bank world regions (see S3 Table). Fisher’s exact test was chosen for its suitability in analyzing small sample sizes and categorical data, as it does not rely on the assumption of large sample sizes required by other tests, such as the chi-squared test. This makes it a good choice for comparing item ratings across subgroups, particularly given the potential variability in panellist numbers across disciplines, income levels, and regions.

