Knowledge users		An adult^a^ who is proficient in English and who is a professional who does not have specialized training or qualifications in wastewater surveillance, but who uses surveillance data to inform policy and action in their workplace.
Engaged public		An adult^a^ who is proficient in English and has relevant lived experience.

Definitions: (1) Professional experience – Paid employment or professional practice in a listed specialization (current or former); (2) Graduate or professional degree – Master’s or Doctor of Philosophy (PhD) relating to a listed discipline subgroup.

a Adult: ≥ 18 years of age

b See S2 Table for specializations associated with each discipline.

We will conduct an all-rounds e-Delphi invitation approach, meaning panellists will be invited to every round regardless of whether they participated in the previous round [37]. Previous Delphi studies have commonly ranged from 20 to 30 panellists; however, there is no agreed upon standard [35,38]. Studies have also shown that the number of panellists and their diversity can impact the quality of outcomes [38]. Therefore, assuming only half of registered panellists will participate in at least one round, we will aim to recruit at least 50 panellists. Preferably, with at least 8–10 people per discipline subgroup. The study working group will monitor the distribution of registered panellists based on their demographic information and will try to distribute appropriately across discipline subgroups and other demographic markers.

Registration to complete the e-Delphi will open approximately four weeks before the first round, and e-Delphi round surveys will be active for roughly 4–6 weeks. The tentative start and end dates for recruitment are 08/09/2025 and 19/12/2025, respectively. Recruitment or retention efforts will occur throughout each e-Delphi round and the four weeks of targeted recruitment before Round 1. Email reminders to complete the survey will be sent twice per e-Delphi round. Panellists may also receive up to two reminders to complete the screening questionnaire during the targeted recruitment period. The time required to complete each e-Delphi round survey will be approximately one hour. The estimated time commitment will be provided to all potential panellists during recruitment and before starting the consensus process.

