### Exclusion of data

All panellists that participate in at least one round will have their responses included in analyses unless the study working group determines that a panellist’s response warrants being excluded from analyses for reasons that are newly developed or not previously recognized.

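### Stability across rounds is to be summarised by group median, range and IQR while the raters may differ between rounds, so a change of panel can be read as a change of opinion

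*Protocol article*

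**What the plan says.** All references are to the protocol article.

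- **Measure.** Quantitative analysis: "We will report response rates, agreement levels, consensus, and stability across rounds using median, range, and IQR for each criterion item". No section restricts stability to people who rated in both rounds, and none names a within-person measure.
- **Who may rate.** Recruitment of panellists: "panellists will be invited to every round regardless of whether they participated in the previous round". Round 2 repeats the rule. Recruitment of panellists adds: "Recruitment or retention efforts will occur throughout each e-Delphi round". That leaves room for new entrants after Round 1 but does not say there will be any.
- **Who is analysed.** Exclusion of data: "All panellists that participate in at least one round will have their responses included in analyses".
- **Which items have two ratings.** Stopping rules: "When consensus is reached for a given item, no subsequent ranking rounds for that item will be performed". Only items without Round 1 consensus are rated again.
- **Linkage.** Round 2: "panellists will be presented with their previous round scores alongside the aggregate group results". A returning panellist's two ratings must therefore be linked in the survey platform.
- **Panel size.** Recruitment of panellists: "assuming only half of registered panellists will participate in at least one round, we will aim to recruit at least 50 panellists".

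**The concern.** A median and IQR for Round 1 set beside a median and IQR for Round 2 are two cross-sectional summaries. They describe change of opinion only if the same people gave both, and even then only the net change.

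Two errors follow for re-rated items. First, if some raters leave and others join, the summaries can move although no individual changed. Second, if individuals move in opposite directions, the summaries can stay still although many changed.

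At stake is what the final report can say about stability, and how a reader interprets a Round 2 result that differs from Round 1. The Limitations section names the influence of feedback on panellists' opinions. Group summaries cannot inform that question, whereas change within the people who saw the feedback could.

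**Working it through.** **1. The plan's own figure.** At least 50 are to be registered, with half taking part in at least one round: 50 × 0.5 = 25 active panellists, or equivalently 25 / 0.5 = 50. The figure reproduces. The article does not say how many will answer each round or both.

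**2. Effect of turnover on percentage agreement when opinions are fixed.** Assumptions: all 25 active panellists rate the item at least once; *n* answer each round; true agreement *p* = 0.60, so that the item plausibly goes to Round 2; turnover is at random.

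The overlap is *m* = 2*n* − 25. Votes of people present in both rounds cancel, so only the 2(*n* − *m*) non-overlapping votes contribute:

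SD of the difference = √[2(*n* − *m*) × *p*(1 − *p*)] / *n*, with *p*(1 − *p*) = 0.24.

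| Answer each round | Overlap | Non-overlapping votes | SD of difference |
|---|---|---|---|
| 25 | 25 | 0 | 0 |
| 20 | 20 + 20 − 25 = 15 | 10 | √(10 × 0.24) / 20 = 0.077 |
| 18 | 18 + 18 − 25 = 11 | 14 | √(14 × 0.24) / 18 = 0.102 |

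The spurious between-round difference thus has an SD of zero with full overlap and about 8 to 10 points in the other two cases. The formula ignores that re-rated items are selected for having missed 70% in Round 1.

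**3. Effect on the median and IQR themselves.** A simulation of 40,000 runs used 25 raters per round and fixed opinions. The assumed probabilities for scores 1 to 7 were 0.03, 0.04, 0.08, 0.10, 0.15, 0.35 and 0.25, which puts 60% in 6–7.

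| Overlap of 25 | Median differs | IQR width differs |
|---|---|---|
| 25 | 0 | 0 |
| 20 | 0.13 | 0.39 |
| 15 | 0.17 | 0.50 |
| 10 | 0.21 | 0.57 |
| 5 | 0.24 | 0.61 |
| 0 | 0.27 | 0.64 |

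With 25 per round, an overlap of 20 implies 25 + 25 − 20 = 30 different people. The rows below full overlap therefore describe a panel larger than the planning figure of 25 and show the pattern only.

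**4. Turnover that is not random (constructed extreme, 40 people).** Ten stayers rate 6 in both rounds, 15 people in Round 1 only rate 4, and 15 in Round 2 only rate 6. The median goes from 4 to 6, the IQR from 4–6 to 6–6, and the share in 6–7 from 10/25 = 40% to 25/25 = 100%. No individual changed.

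**5. Opposing shifts with full retention (constructed, same 25 people).** Eight move from 2 to 6, eight from 6 to 2, and nine stay at 4. In both rounds the median is 4, the IQR 2–6, the range 2–6 and the share in 6–7 8/25 = 32%. Yet 16/25 = 64% changed category. Retention alone does not cure this.

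**The case against.** **The sentence is a compressed list.** Taken literally it would also express response rates and consensus as medians and IQRs, although Defining consensus sets consensus as a percentage. It does not say which raters enter the stability summary, and keeping all one-round participants in the analyses does not rule out a paired subset. This stands in part: group summaries over all raters are the natural reading, not an explicit rule. But the article does name the statistics for stability, and nothing in it points to a paired comparison.

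**Turnover may be small.** Content experts and knowledge users are paid only if they complete all rounds, members of the public enter a draw on the same condition, and two reminders are sent per round. This stands, and it is why the size must be given as a range that starts at zero. It does not touch the opposing-shifts problem.

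**Nothing is decided on stability.** Stopping and classification use only the 70% rule, the number of rounds is fixed at two, and unresolved items go to the consensus meeting. This stands and limits the consequence to reporting.

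**Some of this is disclosed.** Limitations acknowledges the influence of panel composition and of feedback, and response rates will be reported. Response rates show how many answered each round, not how many answered both.

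**Stronger readings a reader might infer.** One is that the 70% decisions are invalid, because a shift of 8 to 10 points can carry an item over the line. The documents do not support this: the rule is defined on the votes cast, the all-rounds invitation is a deliberate choice and not an error, and sensitivity of agreement to who votes is a separate matter from the stability report. Another is that the plan promises a stability figure for every item, including those settled in Round 1. That is over-literal, since Stopping rules makes clear that those items get no second rating.

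**Conclusion.** The point holds in a limited form. As written, the stability report for items without Round 1 consensus can confuse a change of panel with a change of opinion, and can miss offsetting individual changes even with full retention.

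The turnover effect is nil with complete overlap. With 18 to 20 of 25 active panellists answering each round, its SD is about 8 to 10 percentage points of agreement. That range rests on assumed numbers per round, 60% true agreement and random turnover, none of which the article gives. Fewer raters per item are possible, because pathways differ by discipline subgroup and panellists may skip items.

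It cannot be said that turnover will be mistaken for opinion change, only that the planned summaries would not separate the two. The harm is to the stability evidence and the reading of Round 2 results. The consensus rule and the course of the study are unaffected. The change is worth making because the linked data will exist and the cost is small.

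**What to change.** In Quantitative analysis, for items rated in both rounds:

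1. Define stability on panellists who rated the item in both rounds, and report the share who changed category and the within-person change in summary score.
2. Give the number of such raters per item.
3. Report Round 2 agreement for both-round raters as a sensitivity result beside the result for all Round 2 voters. The all-voter result stays the decision rule.

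The per-round median, range and IQR can stay as description. The sponsor should confirm that the data export keeps the anonymous link between a panellist's rounds; no identities are needed.

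Cost: a wording change and a little more analysis code, with no change to recruitment, survey or consensus rule. The paired summaries will rest on smaller numbers, 11 or 15 raters in the two partial-overlap cases worked above, and should be presented descriptively.

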### Qualitative analysis

Content analyses will be conducted on panellists’ feedback to extract common themes and insights. A summary will describe the evolution of each criterion across rounds, including reasons for item modification or elimination.

### Grouping of subgroups

Subgroups with fewer than 5 panellists will be combined with similar groups based on panellist numbers and group likeness. Decisions on combined subgroups will be made prior to analyses of the items.

### Exclusion of data

All panellists that participate in at least one round will have their responses included in analyses unless the study working group determines that a panellist’s response warrants being excluded from analyses for reasons that are newly developed or not previously recognized.

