### Defining consensus

Candidate items will be assessed on the following four rating properties: (1) relevance and practical utility; (2) scientific rigor, validity and reliability; (3) feasibility, adaptability and resource implications; and (4) equity, inclusiveness, and mitigation of bias.

A 7-point Likert scale (1 = highly irrelevant to 7 = highly relevant) will be used to rate each property for all candidate items. A summary score for each candidate item will be created by calculating the median of the four property ratings. Panellist summary scores will then be categorized as excluded item (irrelevant: 1–2), further discussion (equivocal: 3–5), or core item (relevant: 6–7). Consensus for each item is defined as ≥ 70% of the panellist votes falling within the same category (1–2, 3–5, or 6–7).

The approach to use a 7-point fully-labeled Likert scale – a higher number of categories compared to many studies – is informed by the consideration that panellists are professionals and engaged members of the public with good cognitive skills; therefore, more categories and labels will be more discriminating and reproducible [42–45]. The ≥ 70% consensus cut-off – a lower cut-off compared to many studies – is informed by the rapidly evolving nature of environmental surveillance for public health and the wide range of disciplines invited to the panel; therefore, a high level of agreement may not occur [42–45].

The rating properties were synthesized from previous performance evaluation frameworks from public health and health systems [1,24,46–51]. Equity is a property that was not previously identified but was added following an expert group discussion of potential properties and the study’s goals and objectives. See S3 Appendix for further details on the rating properties for e-Delphi candidate item scoring.

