### Ethical considerations

This study has received ethical approval (20230428-01H) from the Ottawa Health Science Network Research Ethics Board (OHSN-REB). Implied consent will be obtained from all panellists prior to participating in the e-Delphi survey. Information about the survey and consent practices will be provided on the first page of the survey. Panellists will be informed that by providing their demographic information and proceeding to the next page, they are providing their implied consent to participate in the study.

Only anonymous panellist responses will be used for analyses. All panellist data and responses will be password protected and only REB-approved study working group members from the Ottawa Hospital will have access to the data.

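### The rule for excluding a panellist's responses has no timing condition and no limit on reasons, and at about 25 raters one exclusion can move a borderline item across the 70% line.

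*Protocol article*

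**What the plan says.** Under Exclusion of data, the default is inclusion of every panellist with at least one round. The exception applies "unless the study working group determines that a panellist’s response warrants being excluded", and the grounds are those under which a "response warrants being excluded from analyses for reasons that are newly developed or not previously recognized". The section gives no list of reasons, no time by which the decision must be made, and no duty to report it.

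Four other sections bear on this:

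- **Ethical considerations:** "only REB-approved study working group members from the Ottawa Hospital will have access to the data".
- **Defining consensus:** "Consensus for each item is defined as ≥ 70% of the panellist votes falling within the same category". The categories are irrelevant (1–2), equivocal (3–5) and relevant (6–7).
- **Stopping rules and Step 4 (Consensus meeting):** an item that reaches consensus is not rated again. The meeting votes on equivocal and non-consensual items.
- **Grouping of subgroups:** small subgroups may be merged, and this is to be settled before the items are analysed. The exclusion rule follows directly and has no matching condition.

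**The concern.** Read literally, the exclusion rule admits only reasons that nobody set down in advance, and the decision lies with people who can see the ratings. E-Delphi responses are anonymous, so a judgement about one panellist would rest largely on that panellist's ratings, comments and non-identifying demographics. Without a timing condition, the decision can be taken when the group already knows which items lie just above or just below the cut-off.

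This matters because consensus is decided by a hard threshold on few votes. One exclusion also removes that panellist's vote from every item they rated, so more than one item could change together. The core list is the product of the study, and a reader of the final framework could not tell whether an item's status depended on a late exclusion.

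**Working it through.** **Inputs**

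- Cut-off: 70% in one category (Defining consensus).
- Recruitment: "we will aim to recruit at least 50 panellists", "assuming only half of registered panellists will participate in at least one round" (Recruitment of panellists).
- Customary size: "Previous Delphi studies have commonly ranged from 20 to 30 panellists" (same section).

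**The plan's own figure.** Registrants needed = active panellists / participation rate. For 20, 25 and 30 active panellists at 0.5 this gives 20/0.5 = 40, 25/0.5 = 50 and 30/0.5 = 60. The stated 50 corresponds to 25 active panellists, the midpoint of the customary range. Choosing the midpoint is an assumption, because the protocol gives only the range. Since 50 is a minimum, 25 is not an upper limit. Since the one-half refers to taking part in at least one round, the number in any single round could also be lower.

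**When one exclusion changes an item's status.** Let k of n raters fall in the leading category.

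- Consensus is gained when a dissenting rater is removed if k/n < 0.70 and k/(n−1) ≥ 0.70.
- Consensus is lost when an agreeing rater is removed if k/n ≥ 0.70 and (k−1)/(n−1) < 0.70.

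| n | Before | After one exclusion | Change |
|---|---|---|---|
| 20 | 14/20 = 70.0% | 13/19 = 68.4% | lost |
| 25 | 17/25 = 68.0% | 17/24 = 70.8% | gained |
| 30 | 21/30 = 70.0% | 20/29 = 69.0% | lost |
| 50 | 35/50 = 70.0% | 34/49 = 69.4% | lost |

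Enumerating every n from 8 to 50 gives exactly one such count at each size. The direction depends on n. At n = 25 only a gain is possible, because 18/25 = 72.0% becomes 17/24 = 70.8% and stays above the line.

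**How often an item sits at that count.** This is the binomial probability of the count, for an assumed true agreement p (the protocol gives none):

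| n | p = 0.60 | 0.65 | 0.70 | 0.75 | 0.80 |
|---|---|---|---|---|---|
| 20 | 12.4% | 17.1% | 19.2% | 16.9% | 10.9% |
| 25 | 12.0% | 16.1% | 16.5% | 12.4% | 6.2% |
| 50 | 4.2% | 9.2% | 12.2% | 8.9% | 3.0% |

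**Why timing matters.** An item at the critical count changes only if the excluded panellist is on the relevant side. At 17/25, 8 of the 25 raters dissent. If the exclusion has nothing to do with the ratings, the chance that a given item changes at p = 0.70 is 0.165 × 8/25 = 5.3%. If the panellist is chosen with the item results in view, the factor 8/25 no longer protects, and every item at the critical count is open to change (16.5%).

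**What happens to an item that changes**

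- Moved into core or excluded consensus: no further rating, and not among the items listed for the meeting vote.
- Moved into equivocal consensus: no further rating, but deliberated at the meeting.
- Moved out of consensus: re-rated in Round 2 if this happens after Round 1, otherwise deliberated at the meeting.

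**The case against.** The strongest reply is that inclusion is the default and exclusion an exception for unforeseen problems. A reader might infer that the group plans to exclude panellists after looking at results. The document does not say so. The access statement is a confidentiality provision, and any team that cleans data has such access. This stands as far as intent goes. It does not answer the point that the rule, followed as written, permits the practice.

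Other tempting readings go too far:

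- **That the stopping rule makes every change final.** It does so only for items pushed into core or excluded consensus. Even for these, the meeting sees each item's score and discusses the rationale for inclusion, though the listed vote does not cover them.
- **That ineligible and duplicate entries are uncontrolled.** The Procedure section has eligibility reviewed before access and gives each eligible person an individual link, which limits both.
- **That items will be decided on a handful of votes.** Survey pathways differ by discipline subgroup, but the protocol does not say that an item goes to only one subgroup. A case such as 6/9 rests on that assumption. A case such as 3/5 becoming 3/4 falls below the floor of five responses set under Summary panellist characteristics.

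It is also true that any cut-off is sensitive to one vote, and that an article may leave detailed exclusion criteria to a fuller plan. But the complaint is not that detail is missing. The article states a rule, and that rule lacks the safeguard given one section earlier for subgroup merging.

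**Conclusion.** The concern holds in a limited form. The rule lets people with access to the ratings exclude responses on grounds not set in advance and at a time of their choosing. With about 25 raters, one exclusion can move a borderline item from 68.0% to 70.8%; at 20, 30 or 50 raters, one exclusion can take an item at exactly 70.0% below the line. Under assumed true agreement of 60% to 80%, about 6% to 17% of items would lie at the critical count at n = 25, and about 3% to 12% at n = 50. These figures treat raters as independent, and the change also requires the excluded panellist to be on the relevant side. The lasting consequence is confined to items moved into core or excluded consensus. This should be corrected before Round 1, but it does not undermine the design and gives no ground for inferring intended misuse.

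**What to change.** Amend Exclusion of data in two respects:

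1. Exclusions rest only on reasons unrelated to the direction of the ratings, and are decided before item-level agreement is computed for that round. This mirrors the condition already set for merging subgroups.
2. For any exclusion decided later, report the number, the reason, and the consensus table with and without the excluded responses, naming each item whose status changes.

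A closed list of criteria is not needed, nor must clearly invalid entries stay in the main analysis. The change works with the anonymity safeguards, because it does not require linking responses to screening records.

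The cost is one or two sentences, one repeated table if a late exclusion occurs, and slightly less freedom to act on problems found late.
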